## Abstract

**Background:**

Compulsive sexual behaviour disorder is a new disorder in the International Classification of Diseases (ICD-11), and is associated with negative consequences in different areas of life. Evidence for pharmacological treatment of compulsive sexual behaviour disorder is weak and treatment options are limited. This proposed study will be the largest and the first randomised controlled trial comparing the efficacy and tolerability of two active drugs in compulsive sexual behaviour disorder.

**Methods and analysis:**

Eighty adult participants with compulsive sexual behaviour disorder according to ICD-11 will be randomised to receive either naltrexone 25–50 mg or fluoxetine 20–40 mg for 8 weeks, followed by 6 weeks without treatment. The study will be conducted in a subspecialised outpatient sexual medicine unit at Karolinska University Hospital, Stockholm, Sweden. The study is financed by grants and entirely independent of the manufacturers.

Exclusion criteria include severe psychiatric or psychical illness, changes to concurrent medication and non-compatible factors contraindicating the use of either drug. The primary outcome measure is the Hypersexual Disorder: Current Assessment Scale (HD: CAS), and tolerability will be assessed by the Udvalg for Kliniske Undersogelser side effect rating scale (UKU), drug accountability, adherence to treatment and drop-out rate. Participants will complete questionnaires at regular intervals, with the main endpoint for efficacy after 8 weeks (end of treatment) and after 14 weeks (follow-up). Blood chemistry will be repeatedly collected as a safety precaution and for research purposes. The results will be analysed using an appropriate analysis of variance model or a mixed model, depending on the distribution of HD: CAS and the extent of missing data.

**Ethics and dissemination:**

The Swedish Ethical Review Authority and the Swedish Medical Products Agency have approved the study on 27 May 2020 and 4 June 2020, respectively (ref. no. 2020-02069 and ref. no. 5.1-2020-48282). Findings will be published in peer-reviewed journals and presented at relevant conferences.

**Trial registration number:**

2019-004255-36

Strengths and limitations of this studyThis is the first randomised controlled trial comparing the efficacy of two pharmacological agents in compulsive sexual behaviour disorder—naltrexone and fluoxetine.The study enables assessment of clinical, psychosocial and biological predictors of treatment response.The lack of placebo-control is a limitation.The study protocol duration of 14 weeks may be seen as limitation of the study design.

## Introduction

Compulsive sexual behaviour disorder (CSBD) is a newly defined diagnosis in the impulse control disorder section of the 11th edition of the International Classification of Diseases (ICD-11).^1^ It entails a persistent pattern of failure to control intense repetitive sexual impulses or urges, resulting in sexual behaviours with negative consequences affecting different areas of life. Adverse consequences associated with CSBD include distress, unwanted pregnancies, sexually transmitted diseases, relationship problems, financial expenses, occupational impairment and risk of crime. Considering these potential severe consequences and the suggested prevalence of 3%–6% of the population,^2^ there is an undisputable, urgent need for effective treatments.

Existing drug studies of CSBD have mainly been case reports and small open-label studies on selective serotonin reuptake inhibitors (SSRIs),^3 4^ antiandrogens^4^ or the opioid antagonist naltrexone.^5–8^ Only one randomised controlled trial has examined the effect of an SSRI (citalopram 20–60 mg/day for 12 weeks) in 28 gay and bisexual men with non-paraphilic compulsive sexual behaviour.^9^ There was no significant difference in the main outcome measure Yale-Brown Obsessive Compulsive Scale-Compulsive Sexual Behavior (Y-BOCS-CSB) score between those assigned citalopram and those assigned placebo.

CSBD and paraphilic disorders are regarded as separate conditions, however, a high level of sexual preoccupation is common in both.^10–13^ To aid physicians in clinical practice, the World Federation of Societies of Biological Psychiatry (WFSBP) has provided treatment guidelines for paraphilic disorders.^14 15^ Psychotherapy is proposed as a first step for low-risk individuals. If results are unsatisfactory, the next step includes SSRIs.

The subsequent levels in the guidelines are for individuals with moderate-high risk for sexual violence and include testosterone-lowering agents such as cyproterone acetate and gonadotropin-releasing hormone agonists. These agents decrease the frequency and intensity of sexual desire and arousal, however use is associated with high rates of adverse effects. Hormonal treatment is potentially unsuitable for help-seeking individuals with conventional CSBD. In order to investigate appropriate pharmacological alternatives, the proposed 14-week randomised controlled trial will compare the efficacy of two active drugs in 80 adults with CSBD. Additional aims are to examine tolerability and what clinical characteristics and biomarkers could be predictors of response.

Based on the WFSBP treatment guidelines and available research,^9^ the SSRI *fluoxetine* will be defined as standard treatment. Alternative treatment will consist of *naltrexone*, an opioid antagonist which prevents reinforcing effects in the mesolimbic reward centre and is used in the treatment of alcohol use disorder.^16^ Naltrexone was chosen due to similarities between CSBD and other urge-driven disorders, and promising results in CSBD case reports, and in our pilot study of 20 men conducted during 2018–2019.^17^ In the latter, all participants completed the 8-week study protocol, and no serious adverse events occurred. Although adverse reactions were common, all were considered mild to moderate, and most were transient during the first days-week. Hence, we were able to determine that naltrexone was a well-tolerated, feasible treatment option and gave indications of symptom relief. However, as the study format prohibited conclusion of efficacy, this study aims to further investigate naltrexone in the treatment of CSBD.

### Primary objective

To compare the effect of naltrexone versus fluoxetine in CSBD.

### Secondary objectives

To investigate if clinical, psychosocial or biological factors can predict treatment response.

To compare if there are any differences in drop-out rate and adherence between the two treatment groups.

To assess side effects and investigate any connection between drop-out rate, reports of side effects and/or efficacy.

To compare if there is a difference in the participants’ wish to resume treatment.

To investigate biological markers and clinical parameters in participants with CSBD.

To investigate correlation between CSBD and impulsiveness, experience of violence and suicidality.

## Methods and analysis

### Study setting and study design

The study will be conducted at ANOVA, a subspecialised sexual medicine outpatient clinic at Karolinska University Hospital in Stockholm, Sweden. Eligible participants will be randomised in blocks with a 1:1 allocation to receive either fluoxetine or naltrexone in a superiority parallel group design for 8 weeks followed by a 6-week follow-up phase. Blinding will not be applicable due to the different appearances of the drugs and dose augmentation in different time intervals due to different pharmacological properties.

### Protocol version

Version identifier: 2.0. Number of protocol amendments: 1; 25 June 2020; main changes included adding blood samples and assessments for safety reasons as requested by the Swedish Medical Products Agency.

### Eligibility criteria

Please see box 1 for inclusion and exclusion criteria.

Box 1Inclusion and exclusion criteriaInclusion criteriaMeet criteria for compulsive sexual behaviour disorder according to ICD-11 and fulfil criteria for hypersexual disorder as originally proposed for inclusion in DSM-5.Between 18 and 65 years.Understand oral and written Swedish and have internet access.Willing to participate in all study visits including providing blood and urine samples.Signed informed consent form.For fertile women: the use of a safe method of contraception during the entire study protocol.Exclusion criteriaSigns of hepatitis, elevated liver enzymes (>3 times over reference) or a history of liver failure.eGFR <60 mL/min, signs or history of acute kidney failure.fp-glucose ≥7.0 mmol/L.Known heart disease such as angina pectoris, previous heart failure or heart attack.Other serious physical illness including diabetes mellitus, epilepsy or known ocular hypertension.Treatment in the past month (≥1 dose) with opioids or benzodiazepines.Treatment in the past month with oral anticoagulants such as warfarin. Intermittent treatment (max. 15 doses per week) with NSAID (eg, ibuprofen) is tolerated.Treatment with tamoxifen.Self-reported use of recreational drugs in the past month or positive drug verification analysis.Alcohol dependence or risk consumption (>14 units of alcohol per week for men, >9 for women) in the past month.Severe psychiatric disorder requiring immediate treatment such as current psychotic disorder or severe depression.Bipolar disorder or history of hypomania.Ongoing treatment with naltrexone or SSRI, or previous hypersensitivity reaction to either.Change of concurrent medication or dosage in the past 3 months regarding antidepressants, ADHD medication, mood stabilisers, antipsychotics, cortisone, testosterone or dopamine precursors. Smaller adjustments may in some cases be acceptable (assessed by study psychiatrist).Ongoing pharmacological treatment with contraindicated substances (eg, tamoxifen and metoprolol).Pregnancy and/or breastfeeding.Mental condition that could negatively influence either the participant’s health or the scientific aspects of the study. High risk for committing sexual offence is included.Ongoing psychotherapeutic treatment.Participation in other studies outside ANOVA.

### Recruitment, randomisation and allocation

The study will be advertised in media and an initial screening regarding compulsive sexual behaviour, and inclusion and exclusion criteria (box 1) will be conducted when potential candidates call the national helpline PrevenTell for individuals with self-identified compulsive sexual behaviour and/or paraphilia. Persons likely to meet criteria for CSBD will receive information about the study and be invited to log into a secure web-based platform to leave a preliminary informed consent and fill in questionnaires.

Participants will thereafter attend a baseline visit at the clinic. After obtaining written informed consent (online supplemental file 1), urine samples will be collected and screened for recreational drug use (eg, amphetamine, benzodiazepines, cannabis, cocaine and opioid) and blood samples will be collected (eg, monitoring of testosterone, luteinizing hormone, glucose, electrolytes and liver enzymes) (table 1). Specific research samples will also be collected (eg, DNA extraction for genome-wide methylation analysis (EPIC) and second-generation DNA sequencing).

10.1136/bmjopen-2021-051756.supp1Supplementary data

**Table 1 T1:** Samples analysed during the study

Screening		
S-FSH	P-ASAT	P-Sodium
S-LH	P-Calcium	
S-SHBG	fP-Glucose	Full blood cell count
S-Testosterone	P-GT	B-HbA1c
S-TSH	P-HDL Cholesterol	
S-T4	P-Potassium	U-screening for substance abuse*
P-Albumin	P-Cholesterol	U-Pregnancy test†
P-ALAT	P-Creatinine	
P-ALP	fP-LDL Cholesterol	Research samples‡
**At 4 weeks**		
P-ALAT	P-GT	Full blood cell count
P-ALP	P-Potassium	
P-ASAT	P-Creatinine	U-Pregnancy test†
P-Glucose	P-Sodium	
**At 8 weeks**		
P-ALAT	P-Creatinine	U-Pregnancy test†
P-ALP	P-Sodium	P-Fluoxetine or U-Naltrexone§
P-ASAT	Full blood cell count	
P-GT	B-HbA1c	Research samples‡
P-Potassium		

*Amphetamine, benzodiazepines, buprenorphine, cannabis, cocaine, fentanyl, methadone, oxycodone, tramadol and other opioids.

†Assigned female at birth only.

‡ E.g. DNA extraction for genome-wide methylation analysis (EPIC) and second-generation DNA sequencing, oxytocin pretreatment and post-treatment.

§Depending on randomisation.

**Table 2 T2:** Study assessments

Objective	Assessments	Measure type	Time point
Assess changes in compulsive sexual behaviours from screening to week 8 and follow-up	Hypersexual Disorder: Current Assessment Scale (HD: CAS)	Outcome	Baseline, weeks 2, 4, 6, 8 and end of study
Assess compulsive sexual behaviours	The Hypersexual Disorder Screening Inventory (HDSI)	Eligibility	Baseline, and end of study
Assess changes in compulsive sexual behaviours from screening to week 8 and follow-up	The Hypersexual Behaviour Inventory (HBI)	Outcome	Baseline, weeks 1–4, week 6, week 8 and end of study
Assess changes in compulsive sexual behaviours from screening to week 8 and follow-up	Sexual Compulsivity Scale (SCS)	Outcome	Baseline, weeks 1–4, week 6, week 8 and end of study
Assess sexual interests	Self-assessment of sexual interests (SSI)	Eligibility	Baseline
Assess sexual dysfunction	International Index of Erectile Function (IIEF)*	Eligibility	Baseline
Assess psychiatric comorbidity	Mini-International Neuropsychiatric Interview (MINI)	Eligibility	Baseline
Assess changes in depression severity from screening to week 8 and follow-up	Montgomery Åsberg Depression Rating Scale—self-rating (MADRS-S)	Outcome safety	Baseline, week 8 and end of study
Assess change of symptoms of depression and anxiety from screening to week 8 and follow-up	Hospital Anxiety and Depression Scale (HAD)	Outcome	Baseline, week 8 and end of study
Assess changes in alcohol use from screening to week 8 and follow-up	Alcohol Use Disorders Identification Test (AUDIT)	Outcome	Baseline, week 8 and end of study
Assess use of drugs	Drug Use Disorders Identification Test (DUDIT)	Eligibility	Baseline
Assess pathological gambling	Gambling Disorder Identification Test (G-DIT)	Eligibility	Baseline
Assess impulsivity	Barratt Impulsiveness Scale (BIS-11)	Eligibility	Baseline
Assess symptoms of attention-deficit/ hyperactivity disorder	Adult ADHD Self-Report Scale (ASRS)	Eligibility	Baseline
Assess history of violence	Karolinska Interpersonal Violence Scale (KIVS)	Eligibility	Baseline
Assess history of childhood trauma	The Childhood Trauma Questionnaire—Short Form (CTQ-SF)	Eligibility	Baseline
Assess suicide ideation and suicidal behaviour throughout the study	Columbia Suicide Severity Rating Scale (C-SSRS)	Safety	Baseline, weeks 1, 4, 8 and end of study
Assess adverse reactions in week 8	Udvalg for Kliniske Undersogelser side effect rating scale (UKU)	Tolerability	Week 8
Question of wanting to resume pharmacological treatment, week 14	Yes/no/do not know option	Outcome	End of study

*Assigned men at birth only.

A psychiatrist will obtain a medical and psychiatric history, perform a physical examination including blood pressure and heart and pulmonary auscultation, as well as perform interviews with the Mini International Neuropsychiatric Interview (MINI)^18^ and Columbia Suicide Severity Rating Scale (C-SSRS).^19^ The study psychologist will focus on sexual behaviours by conducting a structured interview addressing the ICD-11 criteria for CSBD and the Diagnostic and Statistical Manual of Mental Disorders, Fifth Edition (DSM-5) criteria for hypersexual disorder as originally proposed for inclusion^20^ and paraphilia(s). The separate psychiatrist and psychologist interviews aim to determine eligibility criteria in an unbiased manner. If unmatched opinions, the participant will not be included.

The research nurse will open envelopes for randomisation and supply enrolled participants with either naltrexone or fluoxetine accordingly. The allocation sequence is created by an independent investigator at the Karolinska Trial Alliance, a research centre that supports clinical trials. Participants will start treatment if results on blood chemistry are adequate.

The study drugs will be provided by the Karolinska University Hospital’s pharmacy.

Naltrexone (AOP Orphan Pharmaceuticals): initial dose 25 mg per day, and if tolerated will be augmented to 50 mg per day after 3–5 days.

Fluoxetine (Orion Pharma): Initial dose 20 mg per day, and if unsatisfactory symptom reduction and tolerated will be augmented to 40 mg per day after 4 weeks.

In Sweden, The Dental and Pharmaceutical Benefits Agency, a central government agency determines what pharmaceutical product shall be subsidised by the state. The agency also recommends manufacturers for specific drugs based on for example, prize and availability. The manufacturers for naltrexone and fluoxetine in this study were chosen as they were the agency’s recommended product when the application was prepared for submission.

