### Intervention

Figure 1 illustrates study procedures. Participants will assess their symptoms weekly by filling in questionnaires online for example, if they have noticed any change in frequency or intensity of sexual urges or behaviours, how they perceive the treatment and if they experience adverse reactions. Every second week, participants will complete the main outcome measure Hypersexual Disorder: Current Assessment Scale (HD: CAS).^21^ After 4 weeks, new blood samples will be collected, and participants will have a telephone consultation with the study psychiatrist to assess tolerability and psychiatric well-being. Fertile women will be required to conduct a pregnancy test before starting the study and use contraception during the study period. At end of treatment, participants will have a consultation with the study psychiatrist to assess current symptoms of CSBD, psychiatric distress and tolerability. Blood samples will be collected for chemical analysis as well as monitoring drug tablet return and the metabolites of naltrexone respective fluoxetine.

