### Outcome measures

The main outcome is symptom relief as assessed with HD: CAS, which measures symptom severity during the previous 2 weeks according to the suggested conceptualisation of Hypersexual Disorder to the DSM-5.^20^ Corresponding scales for the ICD-11 diagnosis have not yet been developed. We chose a scale that is sensitive to changes and participants will be asked to fill it in at baseline, every second week during the treatment phase and at end of study. However, as the scale is not validated, two additional measures will be used: the Hypersexual Behaviour Inventory (HBI)^22^ and the Sexual Compulsivity Scale (SCS).^23^ Using unpublished data from our research centre, the correlations (Pearson’s) between HD: CAS and HBI were positive at baseline and post-treatment.

We will also analyse factors (clinical, psychosocial or biological) that may be predictors of response, and whether there is any difference in participants’ readiness to resume pharmacological treatment at end of study.

Furthermore, we will also evaluate tolerability using the Udvalg for Kliniske Undersogelser side effect rating scale (UKU),^24^ drug accountability, adherence to treatment, and drop-out rate.

Finally, to aid in understanding CSBD, we will assess for impulsivity, suicidality and childhood adversities, and collect biological markers (eg, DNA and hormones) to evaluate their potential association with CSBD. A summary of assessments and biological markers is presented in tables 1 and 2, and supplemental table (online supplemental file 2). Furthermore, an extension of the study is planned to include neuroimaging data collection.

10.1136/bmjopen-2021-051756.supp2Supplementary data

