### Ethics and dissemination

The study procedures will be carried out in accordance with the Declaration of Helsinki and European Good Clinical Practice Guidelines. The Swedish Ethical Review Authority and the Swedish Medical Products Agency have approved the study (ref. no. 2020-02069 and ref. no. 5.1-2020-48282). The registration of the trial is accessible at https://www.clinicaltrialsregister.eu. Study enrollment started in October 2020.

Eligible participants will be aged≥18 years and understand both oral and written Swedish. Paraphilic interests are not an exclusion criterion, whereas severe risk for sexual violence (as reported in the interviews and questionnaires, eg, participants who report that they actively interact with children for sexual purposes) is.

The study psychiatrists and psychologists are experienced in evaluating and treating patients with CSBD and paraphilic disorders, and the investigators will together decide whether the individual may be a potential study candidate.

The risks for the participants including safety aspects of the drugs have been carefully weighed against the potential benefits of conducting the study, and we believe the latter outweighs the former. The participants’ health and safety will be assessed and prioritised, which may entail discontinuation of treatment. All undesirable medical events that come to our attention will be graded (mild if the symptoms are transient, moderate if temporary medical treatment for relief is needed and severe if hospital care or prolonged medical treatment is needed) and followed until the event is resolved. Serious adverse events and suspected unexpected serious adverse reactions are handled and reported as required by the Swedish Medical Products Agency. The same insurance regulation as in ordinary medical care apply.

Research data from the web-based platform will be stored securely in servers with restricted access. Archived paper material will be stored in a locked cabinet, in accordance with current legislation and regulations. Research samples and data will be destroyed 10 years after declaring end of trial to the Swedish Medical Products Agency.

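### UKU is scheduled only at week 8 and the resume question only at week 14, so both comparisons are conditional on staying in the study

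*Protocol article*

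**What the plan says.** Table 2 of the protocol article gives a time point for every scale. UKU, the only entry typed as a tolerability measure, appears once: "Assess adverse reactions in week 8". The resume item also appears once, at end of study: "Question of wanting to resume pharmacological treatment, week 14". Neither has a baseline or an early-leaver administration in the table. By contrast, MADRS-S and HAD are listed at baseline, week 8 and end of study.

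Under Secondary objectives the plan undertakes "To assess side effects and investigate any connection between drop-out rate, reports of side effects and/or efficacy", and separately to compare the arms on drop-out, adherence and the wish to resume treatment.

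Other sources of side-effect information are described outside Table 2. Under Intervention, weekly online questionnaires ask "how they perceive the treatment and if they experience adverse reactions", and at week 4 there is a "telephone consultation with the study psychiatrist to assess tolerability and psychiatric well-being". Under Outcome measures, tolerability also includes "drug accountability, adherence to treatment, and drop-out rate". Under Ethics and dissemination, "All undesirable medical events that come to our attention will be graded" and followed until resolved. Under Adherence and concomitant care, data already collected from people who leave are kept and analysed. Under Sample size and statistical methods, people who stop treatment stay in the intention-to-treat analysis.

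**The concern.** A scale read once at the end of treatment is observed only in people who are still in the study. If side effects are a reason for leaving, the people most affected have no score, and the arm that loses more of them can look better on that scale. The same holds for a resume question asked only at week 14, because those who found the drug intolerable and left are the ones whose answer is missing.

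Three further points concern UKU:

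- The objective linking drop-out to side effects needs a side-effect measure taken before drop-out. A week-8 score cannot be that.
- Without a baseline, symptoms that arise on treatment cannot be separated from those already present.
- Of the naltrexone pilot's reactions, the Introduction says "most were transient during the first days-week". A single reading at week 8 may come after such reactions have passed.

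Secondary objectives on side effects, drop-out and acceptability are at stake. The primary HD: CAS comparison is not.

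**Working it through.** **1. Planned loss.** The plan gives no figure for UKU or the resume item, so its sample size serves only to supply the expected loss. Inputs from Sample size and statistical methods: difference 3.3, SD 4.74, power 80%, error probability 0.05, with 1:1 allocation from Study setting and study design. Effect size = 3.3/4.74 = 0.696. A two-sided t-test needs 33.4 per arm, which rounds up to 34 and matches the plan. Allowance = 80 − 2 × 34 = 12 participants, and 12/80 = 15%. So about 12 people could lack a UKU score or a resume answer on the plan's own reckoning.

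**2. Who lacks what on the listed schedule.**

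| Participant | UKU at week 8 | Resume answer at week 14 | Weekly reports |
|---|---|---|---|
| Leaves the study before week 8 | None | None | Up to departure |
| Leaves between weeks 8 and 14 | Yes | None | Treatment phase |
| Stops the drug early, stays in the study | Yes, after time off drug | Yes | Not stated to stop |
| Completes treatment and follow-up | Yes, without a baseline | Yes | Treatment phase |

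**3. Effect on the UKU comparison (illustration).** These values are assumed and do not stand in the article: 40 per arm, true side-effect rates of 40% (16 of 40) and 20% (8 of 40), every early leaver is someone with side effects, and affected people who stay still score as affected at week 8.

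Observed rate in an arm = (affected − leavers) / (40 − leavers). The true difference is 20 points.

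| Leavers (worse arm/other arm) | Worse arm | Other arm | Difference |
|---|---|---|---|
| 6/6 | 10/34 = 29.4% | 2/34 = 5.9% | 23.5 points |
| 9/3 | 7/31 = 22.6% | 5/37 = 13.5% | 9.1 points |
| 12/0 | 4/28 = 14.3% | 8/40 = 20.0% | −5.7 points |
| 3/3 | 13/37 = 35.1% | 5/37 = 13.5% | 21.6 points |
| 4/2 | 12/36 = 33.3% | 6/38 = 15.8% | 17.5 points |
| 6/0 | 10/34 = 29.4% | 8/40 = 20.0% | 9.4 points |

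A closer pair of assumed rates, 40% and 30%, with 20% and 10% of the arms leaving because of side effects (8 and 4 people, again 12): (0.40 − 0.20)/(1 − 0.20) = 25.0% and (0.30 − 0.10)/(1 − 0.10) = 22.2%. The difference falls from 10 points to 2.8.

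**4. What the weekly reports would give.** If each affected person reports at least once before leaving, cumulative incidence in the first illustration is 16/40 against 8/40 under every split, so the 20 points are kept.

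**The case against.** A reader might infer that people who leave because of side effects are never measured. The article does not support that. They can report weekly until departure, may have had the week-4 call, have their known events graded, and count in the drop-out rate. Since drop-out and adherence are themselves compared between arms, a drug that drives people out looks worse there. This stands, and it confines the concern to UKU and the resume item.

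A second objection is that stopping the drug is not leaving the study. This also stands: nothing says that people who cease treatment skip week 8 or week 14. They do keep a UKU score, but one taken after time off drug.

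Third, the drop-out objective speaks of reports of side effects, not of UKU, so the weekly reports can already serve it. This is right. The objective is attainable, only not with UKU. However, the article does not name the weekly reports among its tolerability measures, whereas it names UKU first.

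Fourth, the percentages are assumed, and all 20 pilot participants completed the 8 weeks. With no drop-out there is no selection, and with balanced side-effect drop-out the difference hardly shrinks or even grows. At 40 per arm the standard error for 40% against 30% is √(0.4 × 0.6/40 + 0.3 × 0.7/40) = 10.6 points, more than the 7.2-point shift in that illustration. All of this limits the likely size. It does not touch the missing baseline or the timing, and the plan itself allows for 12 losses.

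It would also go too far to say that week 8 misses most reactions or favours one drug. The pilot remark covers naltrexone only, and the article states neither UKU's recall period nor when fluoxetine reactions occur.

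Finally, this is a condensed article. Figure 1, the supplementary table and the full protocol are not shown and may contain an early-leaver assessment. The point therefore rests on the schedule that Table 2 states.

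**Conclusion.** The concern holds in a limited form. On the schedule in Table 2, the UKU and resume comparisons are conditional on staying in the study. UKU cannot separate new from pre-existing symptoms, may miss early transient reactions, and cannot be the side-effect variable for the drop-out objective. Tolerability as a whole is not shown to be biased, because other planned data cover leavers up to departure.

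The size is uncertain. Under the assumed 40% and 20%, with every leaver affected and all 12 allowed losses occurring before week 8, the observed difference runs from 23.5 points (6/6) through 9.1 (9/3) to −5.7 (12/0), against a true 20. Balanced loss distorts it little. Balance cannot be taken for granted in an unblinded comparison of two different drugs, but nothing in the article shows that loss will be unbalanced. Only secondary objectives are affected, and the remedy is cheap enough to be worth adopting.

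**What to change.** Choose one of two routes for side effects:

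- **More UKU readings.** Add UKU at baseline, at the existing week-4 contact, and at the last contact of anyone who leaves early. Report the change from baseline.
- **Use data already planned.** Make the weekly adverse-reaction reports the main between-arm side-effect comparison in all randomised participants, as cumulative incidence, or as worst grade using the article's event grading. Use the reports made before departure for the drop-out objective, and keep week-8 UKU as supportive. Show weeks observed by arm, since reports end when a person leaves.

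For the resume item, compare a yes answer with every other outcome (no, do not know, no answer) among all randomised participants, and give the number of missing answers by arm. This counts people lost for unrelated reasons as not wishing to resume, so the observed answers should be shown beside it.

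The cost is a few extra questionnaire minutes for the first route, and analysis work only for the second route and the resume item. Because enrolment began in October 2020, participants already past baseline cannot supply a baseline UKU, which favours the second route for them.
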